### Reporting and statistical analysis

The reporting of this trial will conform to the reporting guidelines outlined in the Consolidated Standards of Reporting Trials (CONSORT) for non-pharmacological interventions statement of 2010
[25]. The statistical analysis will be by the intention-to-treat principle. The occurrence of the primary outcome (number and frequency of correct ventriculostomy) will be compared between the two randomization groups. The secondary outcome analyses will compare the above-described variables between randomization groups. Subgroup analyses will be performed to evaluate whether other parameters such as age, ventricle size, diagnosis, or experience of the surgeon may influence the results. Data are presented as mean and standard deviation or as median with 25/75 percentiles. Stata version 11.2 StataCorp. 2013. *Stata Statistical Software*, College Station, Texas, United States) will be used for all analyses.

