#### Randomization

The randomization process will start as soon as possible after consent to the study has been obtained. Any patient meeting the inclusion criteria and not violating the exclusion criteria may participate in the VENTRI-GUIDE study and be randomized to either a guided or freehand ventriculostomy. Online randomization will be performed by the treating physician in the study center using permuted blocks, to ensure an equal number of patients in both study arms.

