### Data documentation

The following parameters will be recorded and used to demonstrate successful randomization and the presence of even baseline groups (Table 
1):Age (years);Gender (nominal male/female);Glasgow Coma Score on admission (ordinal, 1 to 15-point scale);Cause of hydrocephalus/slit ventricles Preoperative ventricle size - width (millimeters);Preoperative ventricle size - using the frontal occipital horn ratio (FOHR; millimeters);Preoperative ventricle size - and the width of the lateral ventricle in the coronal plane between the medial wall of the corpus callosum and the septum;Preoperative ventricle size - using the Evans ratio (bifrontal ventricular span, the ratio of maximum width of the frontal horns to the maximum width of the inner table of the cranium; millimeters),Episode of care (nominal, *de novo*/revision) Time from symptom onset to *admissi*on (hours);Time from symptom onset to randomization (hours);Time from symptom onset to EVD (external ventricular drainage placement (hours);Duration of hospital stay (days);Duration of EVD being in place (days);Presence of CSF infection during the first 14 days, as defined by modified clinical diagnostic criteria for device-associated meningitis (treatment required on either positive culture, or elevated cell count, red cell:white cell ratio, increased lactate, and/or decreased glucose (nominal, yes/no) [22].The EVD catheter placed for ventriculoperitoneal shunting (nominal, yes/no).Any associated endoscopic procedure, for example, third ventriculostomy (freetext);Neurosurgical experience of primary operator (years).

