### Sample size analysis

Sample size analysis estimates (hit and miss rates) were based on the results of observational studies. In a recent study of our group on the accuracy of ventricular catheter placement, using anatomic landmarks versus neuronavigation or XperCT-laser guidance, ventricles were hit in 69.2% of catheter insertions (31% miss rate) using anatomical landmarks (non-assisted), as compared to 82.3% with the use of guidance (neuronavigation or XperCT-guidance, *P* = 0.043)
[23]. The placements that were non-assisted were significantly more likely to be extraventricular than those using guidance (odds ratio: 3.73; 95% confidence interval: 1.24 to 11.19; *P* = 0.019). Given data from other retrospective studies on ventricular catheters (in the context of ventriculoperitoneal shunts), similar rates of between 25 and 45%
[4–7] malpositioning are described.

To detect a relative risk of 0.5, which is an absolute risk reduction of 15.5%, 118 patients in each of the two study arms are needed to gain a power of 80%, using a two-sided significance level of 95%. The final planned study size is to include and randomize 236 patients
[24].

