### Factors influencing ventricular catheter placement

There are anatomical, technical, and individual patient- and surgeon-related aspects to consider when placing a ventricular catheter, in particular, ventricular size and choroid plexus distance. Preoperative ventricle size is significant in its relation to the accuracy of catheter placement
[1], which is most relevant in pediatric patients
[27]. Larger ventricles are more likely to have optimally placed catheters, which decreases the risk of proximal obstruction, and hence increases shunt survival. Interestingly, a recent study by Wilson *et al*. in an adult study population (170 patients, mean age 56 years), which is probably comparable to our supposed study group, did not show a correlation of ventricular size by freehand technique (measured as bifrontal ventricular span or by the Evans ratio) with risk of inaccurate placement
[7]. Also the distance to the choroid plexus is described as a factor contributing to catheter occlusion. Ventricular size and choroid plexus distance are related to the first episode of shunt failure, particularly in the pediatric population, because the ventricle size is smaller and the choroid plexus is larger in the pediatric population
[28].

Obstruction, the main cause for shunt failure, may be due to blockage by the choroid plexus, ventricular debris or glial tissue growing into its lumen, or due to reduction in size of the drained ventricle. A retrospective series considering 90 adult and pediatric patients with 116 shunt failures identified as main cause for shunt failure proximal catheter obstruction (38%), followed by infection (29%)
[6]. Mechanical obstruction can be avoided by inserting a sufficiently long catheter with its tip just anterior to the foramen of Monro
[12]. The length, determined in a previous study from the CT scan scout film of the patient, was half of the distance between the external auditory meatus and the midpoint of the coronal suture of the skull, studied in 175 patients, with good results
[12]. Also, Wan *et al*. identified catheter length as a relevant factor in avoiding obstruction. In contrast to their expectations they found, after correcting for age and approach, that a larger catheter (greater than 8.5 cm) was better placed than a shorter catheter

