### Surgical technique

The classical freehand technique uses anatomical landmarks such as the inner canthus and external auditory meatus. The catheter is placed in the anterior horn of the lateral ventricle through a burr hole just anterior to the coronal suture in the mid-pupillary line (approximately 11 cm above the nasion and 3 cm from the midline). It is associated with difficulty in gaining optimum insertion angle and catheter length with better success rates in experienced surgeons. Optimal trajectories for a frontal approach were in the mean 42° in the sagittal plane and 30° in the coronal plane
[5].

The surgical technique using the frontal burr hole as in the present study has the shortest intracerebral route, with more consistent anatomical landmarks
[1]. Others prefer the parietal approach, as the atrium is usually the most dilated part of the lateral ventricle
[5], proposed for patients with expected relevant reduction of ventricular size after shunting
[29]. The frontal and parietal burr holes are associated with better placement compared to occipital burr holes
[1]. In the present protocol, a uniform frontal approach has been chosen.

For difficult implantation situations and/or inexperienced neurosurgeons, other techniques have been described to reduce the rate of malplacements and related complications. Frameless neuronavigational stereotaxy
[4], conventional stereotactic, and robotic-image guidance techniques
[30] (n = 17 patients) used for small or slit ventricles have demonstrated accurate placement of ventricular catheters, however, in relatively small patient groups. Intracranial neuroendoscopy is another alternative in selected cases
[17]. Also real-time ultrasound-assisted catheter placement is used in older children, with the disadvantage of needing a larger burr hole of 1.5 to 2 cm
[15]. There are some disadvantages of these sophisticated methods, such as the prolongation of operative time and dependence on expensive, and sometimes complicated technologies
[18, 31]. Nevertheless, the complication rate might be reduced. In a recent study by our group on the accuracy of ventricular catheter placement using anatomic landmarks versus neuronavigation or XperCT-laser guidance, ventricles were hit in 69.2% of catheter insertions using anatomical landmarks (non-assisted), as compared to 82.3% with the use of guidance (neuronavigation or XperCT guidance, *P* = 0.043)

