### Limitations

Simply monitoring of patients and tracking within a study will already improve performance in most cases, and attention to catheter placement will likely have a similar effect
[19]. In addition, this trial is structured to detect a rather large difference in ventricular misplacements. We are seeking an approximate 15% change, from 35 to 20% hit rate, something which may be very difficult to achieve.

A key limitation is the expected to be an imbalance of surgical skill and/or a learning curve. The surgeons who use the freehand technique will be more experienced using the freehand technique than the mini-tablet-assisted method because they will have performed more procedures using freehand, and we may underestimate the effect size of the guide-assisted method.

In addition, we feel that a learning curve is present, but small because of the similarity between the two procedures. Nonetheless, this limitation is common to surgical randomized controlled trials and will be minimized as best as possible within the limitations of our resources, mostly by doing frequent teaching sessions prior to the opening of the trial. The clinical diagnosis might have an impact on the rate of misplacements with highest rates for suboptimal placements in trauma patients with a midline shift on a CT scan
[21], an effect reducible using randomization, as in the present study.

In conclusion, we have developed a protocol to evaluate if an easy-to-use, portable, image-guided system could reduce the need for multiple passes and improve the rate of accurate catheter placement compared to the standard freehand technique. In contrast with earlier studies, this study is prospective, controlled, and randomized. Considering the high revision rates for patients, especially with small ventricular sizes, the guided technique may lead to better outcome and may be cost-effective. Since the outcome of catheter placement is assessed using an established grading system for catheter tip location post-surgery as the primary endpoint, this study will provide an answer for whether an increase of accuracy for ventriculostomy can be reached in patients with guided ventriculostomy.

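### The stated uses of the baseline predictors leave out covariate adjustment of the primary comparison, which is valid without it but may forgo precision

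*Protocol article*

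**What the plan says.** All references are to the protocol article.

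- **Primary comparison** (Reporting and statistical analysis): "The occurrence of the primary outcome (number and frequency of correct ventriculostomy) will be compared between the two randomization groups". No test or model is named. Under Primary outcome measures, the effect is to be expressed as relative risk, absolute risk reduction and number needed to treat.
- **First use of the recorded variables** (Data documentation): "The following parameters will be recorded and used to demonstrate successful randomization and the presence of even baseline groups". The list includes ventricle size (several measures), cause of hydrocephalus and operator experience. It also includes length of hospital stay, duration of external ventricular drainage (EVD), and cerebrospinal fluid (CSF) infection in the first 14 days.
- **Second use** (Reporting and statistical analysis): subgroup analyses by such factors as age, ventricle size, diagnosis and surgeon experience.
- **Allocation** (Randomization): "using permuted blocks, to ensure an equal number of patients in both study arms". No stratification factor is named.
- **Predictors named in the Discussion:** "Larger ventricles are more likely to have optimally placed catheters" (Factors influencing ventricular catheter placement); "better success rates in experienced surgeons" for the freehand technique (Surgical technique); and "highest rates for suboptimal placements in trauma patients with a midline shift on a CT scan" (Limitations). The effect of diagnosis is left to randomisation. The section on influencing factors also cites a 170-patient adult series, which the authors consider probably comparable, where ventricle size was unrelated to inaccurate freehand placement.

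**The concern.** The article names several drivers of correct placement and collects them, but neither of its two stated uses serves the main estimate. A check of evenness after a sound randomisation answers no trial question, and subgroup analyses ask about effect variation. The use that would sharpen the primary comparison, pre-specified covariate adjustment, is not among those stated.

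The trial has little power to spare. The authors describe the target difference as large and possibly hard to achieve, and the interim look lowers the final significance level. Precision available from data already being collected is therefore worth having.

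The first stated use also has a defect of its own. Hospital stay, EVD duration and CSF infection arise after allocation and may be affected by it, so they cannot show whether randomisation worked.

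**Working it through.** **1. Is the sample size based on an unadjusted comparison?**

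Inputs (Sample size analysis): miss rates 31% and 15.5% (relative risk 0.5, reduction 15.5 points). The stated result is "118 patients in each of the two study arms are needed to gain a power of 80"%, "using a two-sided significance level of 95"%, which I read as two-sided alpha 0.05.

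Formula per arm: n = [1.96·√(2p̄(1−p̄)) + 0.8416·√(p₁(1−p₁) + p₂(1−p₂))]² / (p₁−p₂)²

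- p̄ = (0.31 + 0.155)/2 = 0.2325; 2·0.2325·0.7675 = 0.3569
- 0.31·0.69 + 0.155·0.845 = 0.3449
- n = (1.96·0.5974 + 0.8416·0.5873)² / 0.155² = 115.4, so 116

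With the unrounded 30.8% and 15.4% the result is 117. The stated 118 is thus reproduced to within two patients, with no credit taken for covariates.

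**2. Power at 118 per arm without adjustment.** It is 80.9% at alpha 0.05 and 78.6% at the final-look level of 0.0415 (Interim analyses). Both are single-look figures.

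**3. Gain by approximation.** If covariates explain a share R² of the outcome variance, the effective size per arm is 118/(1−R²). R² is an assumption; the article gives none.

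| Assumed R² | Effective n per arm | Power, alpha 0.05 | Power, alpha 0.0415 |
|---|---|---|---|
| 0 | 118.0 | 80.9% | 78.6% |
| 0.02 | 120.4 | 81.7% | 79.5% |
| 0.05 | 124.2 | 82.8% | 80.7% |
| 0.10 | 131.1 | 84.8% | 82.9% |
| 0.20 | 147.5 | 88.7% | 87.1% |

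**4. Gain by simulation.** Setting: 118 per arm, 31% against 15.5% misses, alpha 0.0415. The adjusted analysis has one prognostic covariate and three pure-noise terms, so the cost of useless covariates is counted. The odds ratios are assumptions.

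| Assumed odds ratio per SD | Variance, adjusted/unadjusted | Power unadjusted | Power adjusted |
|---|---|---|---|
| 1 | 1.02 | 79% | 79% |
| 1.5 | 0.99 | 79% | 80% |
| 2 | 0.94 | 80% | 83% |
| 3 | 0.87 | 80% | 87% |

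A repeat run agreed to within about 0.015 on the variance ratio and about one point on power.

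**5. How many covariates can the data carry?** Expected misses are 118·0.31 + 118·0.155 ≈ 55 at the end and 60·0.31 + 60·0.155 ≈ 28 at the 120-patient interim. A few coarse terms are affordable; a many-category diagnosis variable is not.

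**6. Does chance imbalance add a separate harm?** A factor present in 30% of patients (assumption) can differ between arms by 1.96·√(2·0.3·0.7/118) = 11.7 points. If it changed miss risk by 20 points (assumption), the risk difference would shift by 0.117·20 ≈ 2.3 points. The unadjusted standard error is √(0.3449/118) = 5.4 points and already allows for such shifts.

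**The case against.** The strongest reply is that the article is condensed and the covariate model is routine content of an analysis plan. A reader might infer that the protocol commits to a crude analysis under unstratified randomisation. The text supports neither as a stated fact: it names no model and does not exclude strata, and relative risk, risk reduction and number needed to treat can all come from an adjusted model. This objection stands. What remains is the purpose that the article does state for these variables, and the unadjusted basis of the sample size.

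A reader might also infer that precision is definitely lost, or that chance imbalance would bias the result. Neither follows. The unadjusted comparison is valid and its standard error covers chance imbalance (step 6). The article gives no odds ratio or R² for any predictor. It calls the ventricle-size relation most relevant in children, while this trial enrols adults, and the adult series it cites found none. If that series applies, adjusting for ventricle size would gain almost nothing.

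Nor can adjustment for operator experience be called free of bias. The treating physician carries out the randomisation, and the article does not say that the operator is chosen beforehand. If the operator can change once the arm is known, experience is a post-randomisation variable and adjusting for it can distort the effect.

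Finally, showing comparability in a baseline table is normal practice, and the article specifies no significance test of balance. That is fair, but it does not rescue the variables on the list that arise after allocation.

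**Conclusion.** The point holds as an efficiency recommendation. The article's two stated uses of its predictors do not include the one that could sharpen the primary estimate, and its sample size takes no credit for them. At the final level of 0.0415, adjustment is worth about nothing to one power point for weak predictors (odds ratio per SD up to 1.5), about 3 points at 2, and about 6 to 7 at 3. With covariates of no prognostic value, the variance rises by about 2% and power is unchanged.

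These figures rest on the article's 31% and 15.5% miss rates, on assumed prognostic strengths, and on a single prognostic score standing in for several covariates. The article does not show where in this range the trial falls. Separately, the list meant to show even baseline groups needs correcting, because it contains post-randomisation variables.

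**What to change.** 1. **Primary analysis.** Pre-specify the risk difference, with relative risk and number needed to treat, as standardised from a logistic model. The terms are treatment, one preoperative ventricle-size measure (for example the Evans ratio) and a coarse diagnosis group. Use the same estimator at the interim and final looks.
2. **Operator experience.** Add it only if the operator is fixed before allocation, and say so in the text.
3. **Sensitivity analysis.** Report the unadjusted comparison alongside.
4. **Baseline table.** Replace the aim of demonstrating successful randomisation with a descriptive table of pre-randomisation variables. Report hospital stay, EVD duration and CSF infection with the follow-up data.
5. **Randomisation.** State whether it is stratified. If it is, include the strata in the model.

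The cost is some wording in the protocol or analysis plan and slightly more work in Stata. No new data are needed. The covariates and their coding must be fixed before any outcome data are seen by arm, including at the interim.

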### Interim analyses

This trial will follow a group sequential design, with two stop-points (interim and final analysis; K = 2). The trial will stop if efficacy rules are met. The endpoints assessed at the first stop-point will be based on primary outcomes and adverse events. The first will be the interim analysis which will occur after the accrual of 60 patients in each arm (120 total), thus representing an information fraction of 0.51 at interim analyses. For the efficacy stop-point the commonly used O’Brien-Fleming approach will be used, and a *P* value of 0.0051 at the interim and 0.0415 at the final analysis will be used
[26].

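### The final threshold of 0.0415 is not the two-look O'Brien-Fleming value (about 0.048); the stated pair spends only 4.4% of the 5% alpha and leaves power just under 80%

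*Protocol article*

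**What the plan says.** The Interim analyses section describes the design in full: "This trial will follow a group sequential design, with two stop-points (interim and final analysis; K = 2"). The interim look comes "after the accrual of 60 patients in each arm (120 total"), which the section gives as an "information fraction of 0.51 at interim analyses". It names the boundary, "For the efficacy stop-point the commonly used O’Brien-Fleming approach will be used", and gives its nominal P values as "0.0051 at the interim and 0.0415 at the final analysis will be used". Stopping is for efficacy only.

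The Sample size analysis section says that 118 patients per arm "are needed to gain a power of 80%, using a two-sided significance level of 95"%. This can only mean a two-sided alpha of 5%. The target is a relative risk of 0.5, an absolute reduction of 15.5 points from a 31% miss rate. That section mentions neither the interim look nor a final threshold below 5%.

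**The concern.** Number of looks, timing, boundary family and overall alpha together determine both nominal levels, so the printed values can be checked without any outside source. An O'Brien-Fleming design with one interim look at half information gives up very little alpha early, and its final level should lie just below 0.05. A final level of 0.0415 is much lower than that, although the interim level of 0.0051 is what two looks would give.

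At stake is the number that decides whether the trial succeeds. If the final P value falls between 0.0415 and about 0.048, the named method and the printed threshold give opposite verdicts. A correction made after the data are seen would look like a choice driven by the result. The lost alpha also costs some power, and the sample size makes no allowance for it.

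**Working it through.** **Inputs** (protocol article)
- Interim analyses: K = 2; 60 per arm at the interim, so t = 60/118 = 0.508 (printed as 0.51); nominal P values 0.0051 and 0.0415.
- Sample size analysis: two-sided alpha 0.05; 118 per arm; misses 31% versus 15.5%; power 80%.

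**1. The plan's own sample size.** For a fixed design with pooled variance under the null:

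n = [1.96·√(2·0.2325·0.7675) + 0.8416·√(0.31·0.69 + 0.155·0.845)]² / 0.155² = (1.171 + 0.494)² / 0.0240 ≈ 115.4, so 116 per arm.

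Power at 118 per arm by the same formula is 80.9%. The stated 118 and 80% therefore reproduce as a single-look design at two-sided 5%.

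**2. The named boundary.** Under the null, Z1 and Z2 are bivariate normal with correlation √t. O'Brien-Fleming rejects if |Z1| ≥ C/√t or |Z2| ≥ C, with C solved so that the total rejection probability is 0.05.

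| Boundary | t | Interim P | Final P |
|---|---|---|---|
| O'Brien-Fleming (C = 1.977) | 0.50 | 0.0052 | 0.0480 |
| O'Brien-Fleming (C = 1.979) | 0.508 | 0.0055 | 0.0479 |
| O'Brien-Fleming (C = 1.979) | 0.51 | 0.0056 | 0.0478 |
| Lan-DeMets, O'Brien-Fleming type | 0.508 | 0.0033 | 0.0489 |
| Lan-DeMets, O'Brien-Fleming type | 0.51 | 0.0034 | 0.0489 |
| Lan-DeMets, alternative two-sided form | 0.51 | 0.0061 | 0.0476 |
| Interim held at 0.0051, full 5% used | 0.508 | 0.0051 | 0.0481 |

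The interim value is right for two looks: z rounded to 2.80 gives P = 0.0051. No variant gives a final level near 0.0415. A final level of 0.0415 would use up the full 5% only with an interim level of about 0.0156 at t = 0.508, three times the printed one. For comparison, simulating O'Brien-Fleming with five equally spaced looks gives a final level of about 0.041.

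**3. Type I error of the stated pair.** P = 0.0051 is z = 2.801 and P = 0.0415 is z = 2.038.

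P(|Z1| ≥ 2.801 or |Z2| ≥ 2.038) = 0.0436 at t = 0.50, 0.508 and 0.51.

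Simulating binomial data with the pooled z test, 60 then 118 per arm, gives 0.0433 to 0.0438.

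**4. Power at 118 per arm, 31% versus 15.5%.** The drift is θ = 0.155/SE. SE is 0.0541 unpooled (θ = 2.867) or 0.0550 pooled (θ = 2.818). Z1 has mean θ√t and Z2 has mean θ.

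| Boundary | Pooled | Unpooled | Simulation |
|---|---|---|---|
| Single look at 0.05 | 80.5% | 81.8% | 81.4% |
| Stated 0.0051 / 0.0415 | 78.5% | 79.8% | 79.4% |
| O'Brien-Fleming 0.0055 / 0.0479 | 80.1% | 81.5% | – |
| 0.0051 / 0.048 | 80.2% | 81.5% | 80.9% |

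With the stated pair, 80% power needs 118.5 (unpooled) to 122.6 (pooled) patients per arm, that is 119 to 123. With O'Brien-Fleming it needs 113.6 to 117.6, which 118 covers.

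**5. Results on which the two rules disagree.** Pooled z test, 118 per arm:
- 33 versus 20 misses: P = 0.0426
- 34 versus 21 misses: P = 0.0453
- 40 versus 26 misses: P = 0.0423

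All three pass the two-look O'Brien-Fleming boundary and fail 0.0415.

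**The case against.** The strongest reply is that the error is on the safe side. The threshold is explicit and prespecified, overall type I error is 4.4% rather than 5%, and the trial could be run and read validly as printed. That is correct: no false claim of efficacy becomes more likely.

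The power loss is also small. The shortfall from 80% is 0.2 to 1.5 points, and the planning assumption matters more. The Limitations section describes the target as 35% to 20%; at those rates power is only about 73% to 74% even with 0.048. This stands, and the finding should not be rested on power.

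The cause is unknown. The value is close to a five-look final level, but a one-digit slip is just as possible, and the document supports neither.

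Finally, the article names two primary outcomes and shows no multiplicity rule, so a lower threshold might seem a useful reserve. If either outcome could carry success and the two were independent (both assumptions), familywise error would be 1 − (1 − 0.0436)² = 8.5% with the stated pair and 1 − 0.95² = 9.75% with the full 5% for each. But the article attributes 0.0415 only to O'Brien-Fleming, and the reserve would not control that error anyway. The point does limit one statement: the correction keeps alpha at 5% for each test, not across both outcomes.

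None of these points makes 0.0415 the final level of the named design.

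**Conclusion.** The concern holds. The printed final level contradicts the boundary named in the same sentence: it should be about 0.048. The stated pair spends 0.0436 of the 0.05, so about 0.6 percentage points of alpha go unused. Power at 118 per arm is 78.5% to 79.8%, about 1.6 to 1.7 points below the O'Brien-Fleming pair and marginally below the stated 80% under both variance formulas.

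The main fault is the wrong decision threshold; the power loss is a minor consequence. The result assumes a two-sided overall alpha of 5%, the interim at 60 of 118 per arm, a large-sample test of two proportions, and, for power, 31% versus 15.5% misses. The boundary and alpha figures do not depend on the miss rates.

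**What to change.** Replace 0.0415 with 0.048 and keep 0.0051 at the interim. Alternatively, name the Lan-DeMets O'Brien-Fleming-type spending function and compute both bounds at the information fraction actually reached (about 0.0034 and 0.0489 at 0.51); this also changes the interim level. In either case, state the overall two-sided alpha as 5% and give the power for the chosen boundary. If 0.0415 is intended, the protocol should say why and size the trial for it, at about 119 to 123 per arm under the stated rates.

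The first option is one number, needs no patients beyond 236, and keeps the type I error of the test at 5%. Make the change before any outcome comparison is seen.
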